### Training teachers to deliver the MT programme

The training programme to deliver the MT programme involves teachers first participating in an 8-week MBCT programme, adapted for the general (nonclinical) population, to support the development of their resilience and mindfulness skills (eight 2-h sessions per week, with an all-day mindfulness session supported by a digital app to facilitate mindfulness practice during and after the 8-week course). They will then attend a 4-day training workshop to learn how to deliver the MT in schools, with support where needed when they move onto teach themselves. Within participating schools, as large a pool of teachers as possible will be trained to build in redundancy should teachers either not achieve required levels of competency or leave the school. Training a larger group of teachers will also support greater implementation of the MT programme within the school, outside trial classes, as well as offering peer support throughout the project.

#### Fidelity of the MT programme

To test the effectiveness of the MT programme we need to ensure that it is delivered with fidelity. The teacher training and MT programmes are highly structured and standardised to maximise fidelity. Through teacher selection and teacher training we will endeavour, as far as possible, to ensure that teachers reach an adequate standard before they teach trial classes. During the trial classes, competency/adherence will be monitored. Independent raters will rate a randomly selected subset of videotapes of MT programme classes for fidelity (adherence and competence) using a standardised measure developed by the study team with adaptations made for MT in schools [88, 89].

### Teaching as usual in line with good practice

The trial aim is to establish if MT, when integrated into social-emotional teaching in secondary schools, adds value over and above current good practice. Recent UK Department of Education reports suggest that 60% of secondary schools offer Personal, Social, Health and Economic Education (PSHE) lessons that are ‘good or better’ and that this provision occurs across ages 11–16 years (Key Stages 3 and 4) through a variety of methods including regular scheduled lessons, drop-down days, within other subjects, and in tutor/form time [17, 90]. Determining whether schools have good PSHE provision is challenging. In cohort 1, schools will be eligible for inclusion if their provision of PSHE (or equivalent) meets four criteria: (1) the presence of discrete, regular, named teaching time for PSHE, (2) a named PSHE lead, (3) a written PSHE policy and (4) a named member of the senior leadership team responsible for PSHE. TAU schools will agree not to provide the MT programme (or other curricula that include MT) until study completion. We will conduct a more detailed enquiry into the provision of PSHE in general and social and emotional learning (SEL) elements, in particular at each of the cohort-1 schools (see below), and will use the findings of this to describe provision and modify inclusion criteria for cohort 2 if required. This approach ensures that MT’s effectiveness is tested against current good practice.

### PSHE/social-emotional teaching as usual in both trial arms

Following randomisation, the current provision of social-emotional teaching will be explored using a bespoke tool developed for the MYRIAD trial drawing in part on existing measures [17]. This will enable us to report upon how schools describe their current practice with respect to PSHE in general, and social-emotional teaching in particular, in all randomised schools at the school level and for study pupils within each school and across both trial arms. It will further provide information on how the MT curriculum is integrated into wider teaching provision in intervention schools. This measure will be used initially in cohort 1 and both it, and the initial PSHE eligibility criteria, will be modified if necessary for subsequent cohorts.

### Baseline assessment and follow-ups

Study outcomes will be measured at school consent/baseline (prior to randomisation^1^), preintervention (school term before intervention begins or equivalent), post intervention (within 3 months of the end of the MT programme or equivalent time in the TAU arm), 1-year follow-up (1 year after preintervention measures) and again at 2-year follow-up (2 years after preintervention measures, see Fig. 2). The data gathered from study participants and other sources at each time point are shown in Fig. 2.

**Fig. 2 Fig2:**
[figure not shown]
Standard Protocol Items: Recommendations for Interventional Trials (SPIRIT) diagram detailing trial activities and measures and their timing

### Sample size

The study requires 76 schools in total. All year-7 and year-8 pupils in each participating school (approximately 25,000 in total) will be invited to take part in a baseline assessment. In the subsequent academic year pupils who are members of three or more randomly selected classes (approximately 90 pupils in total per school) will be eligible to participate in the full trial. Thus, approximately 6840 pupils will be eligible to participate in the full trial with the expectation that 5700 will have provided parental consent/pupil assent and 4560 will ultimately complete the trial at 2-year follow-up. Drawing on the two feasibility studies [66, 72], a conservative assumption is made that in each class of 30, 25 children will have consent/assent to participate, and 20 of these will be followed up over 2 years. However, because parental opt-out consent and pupil assent will have been obtained prior to trial class selection where levels of consent/assent are lower than expected, we will have the flexibility to include more classes within a school in order to ensure that the required number of participants (75 in each school) proceed to full trial participation. The 38 schools (clusters) and 2280 children in each trial arm at follow-up (76 schools and 4560 children altogether) is a large enough sample to detect a difference of 0.2 standard deviation units (effect size) on our continuous co-primary outcomes. The sample size has been inflated to allow for multiple testing, setting the two-tailed significance level (alpha) for comparing each individual outcome between the trial arms to 0.0167 to preserve the overall family wide Type I error rate at 0.05. The study has 90% power to detect the specified effect size for each co-primary outcome as statistically significant. The sample size also allows for: (1) clustering of outcomes within schools, assuming an intracluster (intraschool) correlation coefficient (ICC) of 0.04, and (2) 20% dropout, with 60 of the 75 children consenting to participate in the trial providing full follow-up data within each school. Relevant literature suggests that our assumed value of the ICC is conservative. The largest ICC in one of our feasibility studies [66] was 0.037. The ICC for the same measure of depression as used here (CES-D) has been estimated to be 0.033 from a previous study in Quebec based on around 5000 children from across 71 schools drawn from relatively disadvantaged communities [91] and to be 0.009, 0.015 and 0.017 for different year levels (year 8, year 9 and year 10, respectively) based on around 2500 children from across 25 state-funded schools in South Australia spanning the full socioeconomic spectrum [92].

### Outcome measures

Multimethod and multi-informant measures will be used that have reliability, validity and established sensitivity to change, balanced with consideration to minimising burden on both participants and researchers and maximising data quality. All measures will be completed either on paper or via an online system. The pupils will complete the measures in a classroom setting where possible. Details of the measures and the time points at which they are collected are shown in Fig. 2. Where pupils are absent from school on the day at which data are obtained we will liaise with relevant school personnel to determine the most appropriate way of gathering these data, and will endeavour to gather data from as many absent pupils as possible to maximise data completeness.

### Primary outcomes (pupil completed)

Our aim is to determine the effectiveness of the MT programme based on three *co-primary* outcomes at 2-year follow-up: *risk for depression* (Center for Epidemiologic Studies for Depression Scale; CES-D; [64]); *social/emotional/behavioural functioning* (Strengths and Difficulties Questionnaire, youth version; SDQ [93]); and *wellbeing* (Warwick-Edinburgh Mental Wellbeing Scale; WEMWBS [65]). There was consideration of selecting just one primary outcome but the research team, experts in the field who were consulted and peer review concluded that all three co-primary outcomes are critically important. The research team also considered combining the three co-primaries into a composite outcome. However, as the research question includes the specific effect of the intervention on each of the three aspects, not just the overall effect, it was decided to retain the primary outcomes in their natural form. Composite measures can obscure variation that would convey interesting and important information in our proposed work [94].

There are a number of reasons for the choice of primary outcomes. First, adult depression (like mental health generally) is predicted by a range of difficulties in adolescence, including not only low-grade depressive symptomatology, but also social/emotional/behavioural functioning [13, 95–97]. Second, MT is a complex intervention that is specifically designed for young people along the full spectrum of risk/resilience and mental health. The outcome measures, therefore, needed to assess both problems (e.g. depressive symptoms) and also positive mental health. In such instances, and in line with the Medical Research Council (MRC) Complex Interventions Framework [98] and evolving guidance in the literature [99, 100], a number of critical outcomes were chosen as co-primary outcomes that: (1) are targeted by MT, (2) cover the full spectrum of mental health risk/resilience and (3) predict later psychopathology/mental health.

### Secondary outcomes (pupil-, teacher- and school-based)

A range of individual-level *secondary outcome measures* have been chosen based on their value to education policy-makers, school heads and pupils themselves. Secondary outcomes are:Students’ executive functioning (Behaviour Rating Inventory of Executive Function, self- and teacher-rated versions; BRIEF-2 [101])Peer relationships (Resistance to Peer Influence Scale [102])Drug and alcohol use, assessed using a brief measure designed for the studyAnxiety (anxiety subscales from the Revised Child Anxiety and Depression Scale; RCADS [103])Social, emotional and behavioural functioning (Strengths and Difficulties Questionnaire, teacher version [93])Student-level attainment (National Pupil Database [104, 105])Self-harm and suicidal ideation (measured devised for study)Mindfulness skills (Child-Adolescent Mindfulness Measure; CAMM [106])

To support resource allocation decision-making and guideline development by bodies, such as NICE [107], the EuroQol five dimensions measure of health-related quality of life, youth version (EQ-5D-Y) [108], suitable for the calculation of Quality-adjusted Life Years (QALYs) and application to economic evaluation, will also be included, alongside the Child and Adolescent Service Use Schedule (CA-SUS).

Given the high rates of teacher stress and burnout, the importance of school ecology/climate, and the potential of MT to address these variables, the following will also be secondary outcomes:Teachers’ wellbeing (Maslach Burnout Inventory, Educator Survey; MBI [109])Self-efficacy (Teacher’s Self-efficacy Scale; TSES [110])Personal mindfulness (Five Facet Mindfulness Questionnaire, short form; FFMQ-SF, [111])Teacher mindfulness (Mindfulness in Teaching Scale; MTS, [112])Stress (Perceived Stress Scale; PSS [113]),Depression (Patient Health Questionnaire; PHQ9 [114])Anxiety (Generalised Anxiety Disorder; GAD7 [115])

Teacher-level variables will be measured for those teachers within schools identified to teach the intervention prerandomisation, irrespective of which arm of the trial their school is subsequently randomised to. School (cluster)-level outcomes will include school ecology/climate (subscales most relevant to the intervention from the School Climate and Connectedness Survey (SCCS) [116]) and school-level attainment; for example, GSCE results (National Pupil Database).

Study outcomes will be measured at five time points: baseline (school and teacher as well as primary measures for all pupils from years 7 and 8); preintervention (school term before intervention or equivalent); 3 months post intervention (or equivalent); 1 year (1 year after preintervention) follow-up; and again at 2-year follow-up (2 years after preintervention). It is important that outcomes are measured over a short enough period to enhance data completeness as well as over a long enough period to examine emergent risk/resilience over time.

### Economic data

The economic evaluation will take a health and social care perspective, as preferred by NICE [107], but will additionally include education-based services, since evidence suggests that health and education make up the majority of the costs of caring for young people with depression [117].

Service use will be recorded using a brief version of the Child and Adolescent Service Use Schedule (CA-SUS), successfully applied in previous adolescent depression populations [117]. A brief version focussing on key services (high cost and high volume of use), suitable for self-completion by parents of primary school children, is currently being applied in a similar school-based cluster RCT [73]. This measure will be adapted for application to an older population and for self-completion by the young people. Economic data will be collected at pre and post intervention as well as at 1- and 2-year follow-up. The preintervention measure will collect information covering the previous 3 months; at follow-up the service use will be recorded for the period since the most recent prior assessment of this data .

Resource inputs into MT training and delivery will be recorded as part of the trial and will be costed using a micro-costing approach. This will involve calculation of the cost of all individual elements (teaching and training staff time, any supply teaching expenses, training and intervention materials, etc.), as well as relevant overheads (administration, managerial, capital, etc.) and adjustment for indirect time (non-face-to-face working time which cannot easily be allocated to specific individuals). All other services used will be costed by applying nationally applicable unit costs, including National Health Service reference costs for secondary care services, as well as published costs for primary care, social care and education services [118].

Outcomes for the economic evaluation will be measured using the youth version of the EQ-5D measure of health-related quality of life (EQ-5D-Y) [108], shown to be valid and responsive to change in adolescent populations [119].

### Analysis plan

Analyses will be conducted/supervised by the co-investigator trial statistician ([name]) and trial health economist ([name]) and reported following CONSORT standards, overseen by the Data Monitoring Committee (DMC) and documented in a full prespecified statistical analysis plan. Analyses will be conducted on an intention-to-treat basis, with participants analysed according to the trial arm that they were randomised to, using multiple imputation to ‘fill in’ missing data. Comparisons will also be made between the trial arms, based on those with complete data in a sensitivity analysis. All between-arm comparisons will be run first as crude (unadjusted) analyses and then adjusted for baseline prognostic factors, chosen a priori, but certainly including the factors used to stratify the randomisation and, where measured, the baseline score of the outcome variable. The adjusted analysis will be considered to be the main analysis.

The approach to evaluating the intervention emphasises estimation of the intervention effect (confidence intervals), rather than strictly hypothesis testing. In recognition of the multiple testing, we will use an adjusted critical level for significance testing of 0.0167 for each of the three primary outcomes at 2 years to maintain the overall Type I error rate at 0.05. The confidence intervals will not be adjusted for multiple comparisons. No adjustments will be made to the critical levels for testing the primary outcomes at the earlier follow-ups, nor the secondary outcomes, as these are more exploratory in nature. The study sets out to establish the superior effectiveness and cost-effectiveness of MT compared with TAU. As set out above, all the co-primary outcomes are deemed important in their own right, such that each will be reported independently.

The main reported clinical analysis will use the intention-to-treat principle. The definition of a trial participant will be those who provide data at the baseline assessment and are subsequently in the classes randomly selected for participation in the full trial. In ancillary exploratory analyses we will also examine whether the effectiveness of the intervention is greater for schools, teachers and pupils that adhere to the curriculum (i.e. engage with intervention and, in the case of pupils in the MT arm, use the mindfulness practices). Because adherence is likely to be associated with factors that impact on the outcomes, we will account for this confounding using instrumental variable methods [120].

All analyses will account for clustering within schools as this is a cluster-randomised design. Continuous outcomes will be compared using random effects (‘multilevel‘) linear regression and binary outcomes will be compared using marginal logistic regression models using Generalised Estimating Equations (GEEs) with information sandwich (‘robust’) estimates of standard error, specifying an exchangeable correlation structure within clusters. Continuous outcomes will be summarised for each trial arm using means and standard deviations and binary outcomes will be summarised for each trial arm using numbers and percentages.

We will use tests of interaction to explore potential moderators of outcome, including, but not exclusive to: school level deprivation (proportion of pupils eligible for free school meals); the children’s age/year group; baseline risk for depression; wellbeing; and strengths and difficulties (SDQ). The latter is particularly important, as it is key to engagement with MT. These analyses are exploratory and hypothesis-generating in nature [121]. We acknowledge the issue of multiple testing and the need to cautiously interpret significant findings that will require replication in subsequent studies to have credence. We also acknowledge the low statistical power of tests of interaction in comparison to the power for detecting main effects [122].

Whilst mechanisms of action and potential mediators are examined in detail in a separate programme of work, we will explore potential mechanism variables pre and post MT in both trial arms and key outcomes at 1- and 2-year follow-up. We will ask if the change in mechanisms is specific to MT, changes as a function of use of mindfulness skills, precedes changes in the outcomes, and explains changes in key outcomes at follow-up. We will examine whether such changes occur over and above changes in those outcomes from baseline to post treatment [123] and through moderated mediation explore what works for whom. Methods for the analysis of mediation using clustered data are in the infancy of their development [124]. We will keep abreast of ongoing methodological research in this area and these analyses will be both exploratory and hypothesis-generating in nature.

Cost-effectiveness will be assessed in terms of QALYs using the EQ-5D-Y. Secondary analyses will explore cost-effectiveness in terms of the three co-primary outcomes to assess the sensitivity of analyses to the alternative outcomes of interest. We will employ standard methods of analysis, including multiple imputation for missing data, adjustment for baseline prognostic factors in line with the clinical analyses, and standard parametric tests for differences in costs, with the robustness of the parametric tests confirmed using bias-corrected, nonparametric bootstrapping [125]. Cost-effectiveness will be assessed using the net benefit approach, with uncertainty explored through the presentation of cost-effectiveness acceptability curves [126]. A within-trial analysis will be undertaken at 2-year follow-up.

The lifestyle choices and behaviour of young people on the threshold of adulthood can lead to short- and long-term adverse outcomes that are expensive for society and damaging to themselves [127, 128]. To this end, longer-term outcomes and costs will be explored using decision analytic modelling [129]. The model will be populated using data from our ongoing programme of work, including trial data and research on teacher training models, as well as evidence from the literature and relevant longitudinal cohort databases. The most suitable modelling framework in which to carry out the analysis will be dependent upon the results of the RCT, and thus will be finalised at a later point. Markov modelling is likely to be the most appropriate for extrapolation over the longer term since it is able to deal with relatively complex care pathways. The cost-effectiveness model will be analysed using incremental analysis and probabilistic sensitivity analysis. The time period over which the model will be run will be determined after review of the literature, since data availability is the key limiting factor. These analyses are exploratory and hypothesis-generating in nature [121].

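### A fixed 0.0167 for each of the three co-primary outcomes is valid, but Holm's step-down would use the chosen 5% familywise error more efficiently at no cost in sample size

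*Protocol article*

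**What the plan says.** The protocol article has three co-primary outcomes at 2-year follow-up: CES-D, SDQ and WEMWBS. The Analysis plan fixes the testing rule: "we will use an adjusted critical level for significance testing of 0.0167 for each of the three primary outcomes at 2 years". The Sample size section uses the same rule, "setting the two-tailed significance level (alpha) for comparing each individual outcome between the trial arms to 0.0167", with the purpose "to preserve the overall family wide Type I error rate at 0.05". No step-down, step-up or gatekeeping procedure is mentioned.

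Each outcome can support its own claim: "all the co-primary outcomes are deemed important in their own right, such that each will be reported independently". Under Primary outcomes, a composite is rejected because the research question covers the specific effect on each of the three.

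The Analysis plan also leaves the confidence intervals unadjusted for multiplicity and gives estimation more weight than strict testing.

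On power, the Sample size section claims: "The study has 90% power to detect the specified effect size for each co-primary outcome as statistically significant".

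**The concern.** The protocol wants a separate answer on depression risk, behavioural functioning and wellbeing, so power for the second and third outcomes matters as well as power for the first. Under the fixed rule each outcome is held to 0.05/3 whatever the others show. Once one outcome is significant, that is stricter than a 5% familywise limit requires.

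Holm's procedure respects the same limit. Suppose m of the three null hypotheses are true. When the first true null comes up for testing, at most 3 - m false ones have been rejected before it, so its threshold is at most 0.05/m. By the Bonferroni inequality over those m nulls, the chance of any false rejection is at most 0.05, whatever the correlation. Every p-value that passes 0.0167 also passes under Holm.

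At stake are real effects on a second or third outcome with p-values between 0.0167 and 0.05, which the current rule would not call significant.

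**Working it through.** **Inputs from the Sample size section.** Effect 0.2 SD; two-sided alpha 0.0167; power 90%; 38 schools and 2280 followed-up pupils per arm, hence 2280/38 = 60 per school; "assuming an intracluster (intraschool) correlation coefficient (ICC) of 0.04". The correlation between the three outcomes is not given, so I assume 0 to 0.7.

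**Step 1: reproduce the plan's figure.**
- Without clustering: n per arm = 2 × (2.393 + 1.282)² / 0.2² = 675.2, rounded up to 676.
- Design effect: 1 + (60 - 1) × 0.04 = 3.36.
- 676 × 3.36 = 2271 per arm; 2271/60 = 37.9, so 38 schools per arm.
- Recruited: 4560/0.8 = 5700.
- Standard error at 2280 per arm: √(2 × 3.36/2280) = 0.0543 SD. Noncentrality: 0.2/0.0543 = 3.684. Power at 0.0167: Φ(3.684 - 2.393) = 90.2%.

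The stated design reproduces.

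**Step 2: power for one outcome at each Holm threshold (effect 0.2 SD).**
- 0.0167: 90.2%
- 0.025: Φ(3.684 - 2.241) = 92.5%
- 0.05: Φ(3.684 - 1.960) = 95.8%

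**Step 3: compare the two rules.** I simulated three equicorrelated normal test statistics with the standard error above, at least 1,000,000 draws per scenario. Ranges run over correlations 0 to 0.7.

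| True effects (SD) | Quantity | Fixed 0.0167 | Holm |
|---|---|---|---|
| 0.20, 0.20, 0.20 | power per outcome | 90% | 94-95% |
| 0.20, 0.20, 0.20 | power for all three | 73-81% | 88-90% |
| 0.15, 0.15, 0.15 | power per outcome | 64% | 71-74% |
| 0.20, 0.20, 0 | power per real effect | 90% | about 92% |
| 0.20, 0, 0 | power for the real effect | 90% | 90% |
| any of the above | at least one rejection | same | same |

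**Step 4: error rates.**

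| True effects (SD) | Error | Fixed 0.0167 | Holm |
|---|---|---|---|
| 0, 0, 0 | familywise | 3.9-4.9% | 3.9-4.9% |
| 0.20, 0, 0 | familywise | 2.9-3.3% | 3.8-4.8% |
| 0.20, 0, 0 | each null outcome | 1.7% | 2.5% |
| 0.20, 0.20, 0 | the null outcome (= familywise) | 1.7% | 3.9-4.6% |

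The top of the last range can be checked by hand at zero correlation. The null outcome is rejected in three cases:
- its p is at most 0.01667;
- its p lies between 0.01667 and 0.025 and at least one other outcome passes 0.01667, with probability 1 - (1 - 0.9015)² = 0.990;
- its p lies between 0.025 and 0.05, both others pass 0.025 and at least one passes 0.01667, with probability 0.9254² - (0.9254 - 0.9015)² = 0.856.

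Total: 0.01667 + 0.00833 × 0.990 + 0.025 × 0.856 = 0.0463.

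**The case against.** The plan is consistent. Both sections use 0.0167, the sample was sized for it, and it gives the promised 90% per outcome. A reader might infer that the trial is underpowered or its multiplicity control faulty. Step 1 shows neither is so.

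A reader might also infer that the stricter threshold buys no error protection at all. That is exact only when all three effects are null. With two real effects the fixed rule falsely claims the null outcome in 1.7% of trials, against 3.9-4.6% under Holm. The extra power is partly paid for in this way. What answers the point is that the protocol chose 0.05 as its familywise limit, and Holm stays inside it.

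The fixed rule gives each outcome a verdict independent of the other two. Under Holm, whether p = 0.03 counts as significant depends on the other p-values. Given the wish to report outcomes independently, this is a fair reason to hesitate, and it stands as a small cost.

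The gain is also conditional. It needs at least two real effects. Power for all three is not a success criterion in the protocol, so that row of the table only illustrates. The Sample size section calls its ICC conservative; at the 0.033 it also cites, power per outcome at 0.2 SD with correlation 0.5 to 0.7 goes only from 93.8% to 96.5-96.8%. Baseline adjustment could narrow the gain at 0.2 SD further. The emphasis on estimation lowers the weight again, since Holm alters no estimate and no interval.

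The usual reason to keep Bonferroni is its matching simultaneous intervals. That does not apply here. A reader might suppose that 98.33% intervals accompany the 0.0167 threshold, but the Analysis plan leaves intervals unadjusted.

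**Conclusion.** The concern holds as an efficiency point. The fixed threshold is valid but uses less of the 0.05 error allowance than it could once one outcome has succeeded. Holm would add about 4 to 5 percentage points of power per outcome if all three effects are 0.20 SD, 7 to 10 points if all are 0.15 SD, about 2 points if two are 0.20 SD and one is null, and essentially nothing if only one is real. The chance of at least one significant outcome is identical.

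These sizes rest on the protocol's ICC of 0.04, 60 pupils followed up per school, a normal approximation and an assumed correlation of 0 to 0.7. That Holm keeps familywise error within 0.05 and never rejects less than Bonferroni needs none of these assumptions. The change is optional.

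**What to change.** Before unblinding, replace the fixed-threshold sentence in the Analysis plan with one stating that the three 2-year co-primary outcomes will be tested by Holm's step-down procedure at a two-sided familywise level of 0.05. The smallest p-value is compared with 0.0167, the next with 0.025 and the largest with 0.05, stopping at the first that fails. Report Holm-adjusted p-values: 3 × the smallest, 2 × the middle and 1 × the largest, each capped at 1 and never lower than the one before.

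Keep the sample size calculation. Holm's first step is still 0.0167, so 90% per outcome becomes a lower bound under the same assumptions. Keep the unadjusted confidence intervals already planned.

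The cost is one sentence and no additional schools or pupils. The text should acknowledge that an outcome's significance label then depends on the other two p-values, and that the chance of a false claim on a single null outcome is somewhat higher, within the 0.05 limit.
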